## Abstract

**Background:**

There are a number of gaps in the evidence base for the use of ankle-foot orthoses for stroke patients. Three dimensional motion analysis offers an ideal method for objectively obtaining biomechanical gait data from stroke patients, however there are a number of major barriers to its use in routine clinical practice. One significant problem is the way in which the biomechanical data generated by these systems is presented. Through the careful design of bespoke biomechanical visualisation software it may be possible to present such data in novel ways to improve clinical decision making, track progress and increase patient understanding in the context of ankle-foot orthosis tuning.

**Methods:**

A single-blind randomised controlled trial will be used to compare the use of biomechanical visualisation software in ankle-foot orthosis tuning against standard care (tuning using observation alone). Participants (n = 70) will have experienced a recent hemiplegia (1-12 months) and will be identified by their care team as being suitable candidates for a rigid ankle-foot orthosis. The primary outcome measure will be walking velocity. Secondary outcome measures include; lower limb joint kinematics (thigh and shank global orientations) & kinetics (knee and hip flexion/extension moments, ground reaction force FZ_2 _peak magnitude), step length, symmetry ratio based on step length, Modified Ashworth Scale, Modified Rivermead Mobility Index and EuroQol (EQ-5D). Additional qualitative measures will also be taken from participants (patients and clinicians) at the beginning and end of their participation in the study. The main aim of the study is to determine whether or not the visualisation of biomechanical data can be used to improve the outcomes of tuning ankle-foot orthoses for stroke patients.

**Discussion:**

In addition to answering the primary research question the broad range of measures that will be taken during this study are likely to contribute to a wider understanding of the impact of ankle-foot orthoses on the lives of stroke patients.

**Trial registration number:**

ISRCTN: ISRCTN52126764

## Background

### Post-stroke AFO use

There is currently a limited amount of published evidence that a rigid ankle-foot orthosis (AFO) fitting can improve mobility and indirectly quality of life for stroke patients [1-3]. While assessment for AFO in stroke patients is recommended, the grade of recommendation in recently published Scottish Intercollegiate Guidelines Network (SIGN) clinical guidelines remains low [4]. This low grading of recommendation reflects the lack of evidence on the impact of AFO on both functional and long-term outcomes. It was also noted that there was insufficient evidence regarding the comparative effects of different types of AFO. Guidance on screening and assessment for the provision of AFO for stroke patients is now available in an NHS Scotland Best Practice Statement [5].

### AFO tuning

AFO tuning involves making small dimensional changes at the foot and ankle that can have a significant positive biomechanical effect at the knee and hip in children with cerebral palsy [6-9]. Appendix 7 of the NHS BPS [5] provides guidance on how to tune an AFO effectively for stroke patients. Given the supposed important role of AFO tuning, it is surprising that in previous AFO stroke studies there are limited descriptions of the AFOs used in terms of; position of leg during casting or scanning, materials used, tuning process followed (if any) and heel wedge sizes.

While the majority of AFO tuning studies have considered children with cerebral palsy, one describes a case study with a stroke patient [10]. The authors found that AFO tuning did have a positive effect on stride length and a reduction in knee hyperextension.

### Gait analysis

Observational gait analysis has been shown to be ineffective and unreliable [11,12] while computerised 3D gait analysis results have been shown to have a significant impact on clinical decision making [13,14], thus strengthening the argument for the use of objective computerised gait analysis techniques. Despite computerised gait analysis being shown to have a significant impact on surgical decision making there are a number of perceived barriers to its use. Baker described many of these barriers and identified the interpretation of clinical gait data as being a significant problem [15]. Furthermore, Coutts stated that "interpretation of biomechanical data is complex, time consuming and not readily understood by most therapists" [16]. Other barriers include the cost of the motion analysis equipment, the high level of technical expertise required to operate it and the time needed to collect patient data. Physiotherapists and orthotists in the UK rarely have access to computerised 3D gait laboratories to assist with their clinical decision making [17].

Physiotherapists and orthotists play pivotal roles in the multi-disciplinary team (MDT) approach advocated by the NHS BPS [5] and in the context of AFO tuning there is a clear need for a method of making biomechanical gait data easier to understand through having a user-friendly interface and a rapid presentation of key gait parameters. One study found that there were significant inter-disciplinary differences in how gait data is analysed [17], so there is a need for a common gait analysis language that can be understood by a range of healthcare professionals.

### 3D motion analysis and AFO tuning

The results of a pilot study where a rigorous biomechanical approach to AFO fitting and tuning was used, with ten stroke patients, showed that correct use of AFOs improved a number of important gait characteristics [18]. The results showed significant improvements in ground reaction force (GRF) vector alignment at the hip and an increase in step length for the affected limb as well as an overall increase in walking velocity. Other improvements were also found in GRF alignment at the knee, step length and knee extension of the unaffected limb. Given the small sample sizes used in the pilot study, the more powerful study described here is justified.

Previous work in the area of visualising biomechanical data has shown that animation techniques can enhance both older adult, health professional and design professionals' understanding of the biomechanics of everyday tasks [19]. Given the complex biomechanical nature of AFO tuning, it follows that this activity could benefit from the use of 3D motion analysis combined with a biomechanical visualisation tool (to interpret the data). This may help the MDT administering the treatment package and subsequently improve patient outcomes.

This study constitutes one part of a wider project called **en**vis**age**. The **en**vis**age **project will investigate the use of visualisation software to help communicate biomechanical data in a variety of rehabilitation settings. The project represents a multidisciplinary collaboration between the University of Strathclyde, The Glasgow School of Art and Glasgow Caledonian University.

### Primary research question

Does visualisation of biomechanical data improve the outcomes of tuning ankle-foot orthoses (AFOs) for stroke patients?

### Secondary research questions

1. Can biomechanical visualisation enhance orthotists' and physiotherapists' understanding of biomechanics?

2. Could a visualisation tool facilitate better communication between the members of the multidisciplinary team?

3. Does a patient's understanding of their own biomechanics and corresponding treatment programme change when a visualisation tool is used?

4. Can a database of anonymous gait data on the effects of AFO on stroke patients be created?

## Methods/design

### Study design - Single-blind RCT

The null hypothesis of the study is that there is no difference in outcome measures for stroke patients between observation-based AFO tuning and objective AFO tuning with 3D motion analysis and biomechanical visualisation software. The alternative hypothesis is that objective AFO tuning with biomechanical visualisation software improves outcome measures for stroke patients.

A single-blind randomised controlled trial (RCT) methodology has been selected to test this hypothesis as shown in Figure 1. The patients will be blinded as to the intervention they will be given, however the clinicians involved will not be blinded. The independent assessor conducting the statistical analysis on the main trial outcome measures will also be blinded. The main benefit of using an RCT is that any potential selection bias and confounding factors will be minimised.

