**Figure 1 F1:**
[figure not shown]
**Flow diagram of trial design showing intervention (visualisation) and non-intervention (observation) arms**.

The randomisation sequence will be generated using an independently verified S-PLUS program, by the method of randomised permuted blocks of length four, with participants allocated to interventions in a 1:1 ratio. Researchers will access the random allocations via the study web portal (designed and maintained by The Robertson Centre for Biostatistics at The University of Glasgow) and the sequence will remain concealed until the participant's details are registered on the system.

As patients are recruited to the trial they will be randomly allocated to one of two multidisciplinary teams (MDTs). Each of these MDTs will be made up of a physiotherapist, orthotist and bioengineer. MDT-A will administer the intervention arm of the study, MDT-B will administer the non-intervention arm. In the intervention arm patients will be shown visualisations of their gait patterns and progress throughout the trial. Additionally, the clinicians in MDT-A will also be able to use the gait data and visualisation software to aid their clinical decision making during the AFO tuning session. MDT-B will conduct AFO tuning using standard observational techniques.

Baseline, outcome (3 months) and follow-up (6 months) measurement sessions will be collected by the bioengineer and a third physiotherapist who is independent of the MDTs.

All clinical decision making will be carried out by the physiotherapists and orthotists, while the bioengineer will play a purely technical role collecting data and presenting it to the clinicians and the patient when it is required. The same bioengineer will be used in both MDTs and will be present during all sessions.

Ideally both MDTs would be identical, but this is clearly not possible. Two different MDTs are needed to avoid learning effects in the intervention arm of the study crossing over to the non-intervention and confounding results. In order to balance the MDTs, team members will be selected such that they have similar levels of experience and they will all be required to complete a small amount of basic biomechanics refresher training before the trial commences.

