#### Baseline

All patients will have baseline gait measurements taken using a 3D motion analysis system. After measurements have been taken, patients in the intervention arm will additionally be shown relevant visualisations which will help to explain and quantify their gait problems.

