### Statistical Analysis

Quantitative data from the four patient measurement sessions (baseline gait, AFO tuning, three and six month gait) will be analysed on an 'intention to treat' basis. Data will be held independently on a bespoke database at the Robertson Centre for Biostatistics at the University of Glasgow, and independent assessors comparing data sets will be blinded as to which arm of the trial each patient was allocated to.

The primary emphasis of the statistical analysis will be on between-group differences to establish if differences in outcome measures are apparent. This will be achieved using two-way repeated measures ANOVA analysis, followed by a series of post-hoc tests which are most likely to be t-tests.

All data will be tested for normality, and where normality does not occur the equivalent nonparametric tests will be used instead. A significance level of 0.05 will be used and a Bonferroni correction will be used when multiple t-tests are required. Qualitative data obtained from the various interviews will be collated and a suitable coding system established such that the responses can be categorised.

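### Patients are stated to be blinded, but only the intervention arm is shown gait visualisations; one outcome collector knows the arm, the other is not stated to be blinded, and only the analysis is stated to be blinded

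*Protocol article*

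**What the plan says.** **Label.** The protocol article, section Study design - Single-blind RCT, states that "A single-blind randomised controlled trial (RCT) methodology has been selected to test this hypothesis". It defines the blinding as follows: "The patients will be blinded as to the intervention they will be given, however the clinicians involved will not be blinded".

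**Analysis.** The same section adds: "The independent assessor conducting the statistical analysis on the main trial outcome measures will also be blinded". The Statistical Analysis section repeats the point: "independent assessors comparing data sets will be blinded as to which arm of the trial each patient was allocated to".

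**What patients see.** The text after Figure 1 says: "In the intervention arm patients will be shown visualisations of their gait patterns and progress throughout the trial". The Baseline section says that, once measured, "patients in the intervention arm will additionally be shown relevant visualisations which will help to explain and quantify their gait problems". The 3-month and 6-month sections add a progress discussion using visualisations, again for the intervention arm only.

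**Who collects outcomes.** The text after Figure 1 says of the baseline, 3-month and 6-month data that the "measurement sessions will be collected by the bioengineer and a third physiotherapist who is independent of the MDTs". It says of the bioengineer: "The same bioengineer will be used in both MDTs and will be present during all sessions". The bioengineer also presents the data to clinicians and patients.

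**The concern.** The blinding statement and the description of the intervention cannot both be true. A patient who is shown displays of their own gait knows that they received the visualisation arm's treatment, and the document says patients are blinded to exactly that.

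This matters because of the outcomes chosen. Walking velocity is a volitional measure: it can respond to how hard the patient tries and to how the person running the test encourages them. EQ-5D is self-reported, and the Modified Ashworth Scale and Modified Rivermead Mobility Index are scored by a rater. Blinding the analyst protects none of these, because the data already exist by then. If the patient and at least one collector know the arm, a difference can arise that is not due to better tuning, and a report that repeats the single-blind label would describe the trial wrongly.

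**Working it through.** **1. Patient level, in time order.** From the AFO scanning and fitting, Baseline, Tuning, 3-month and 6-month sections:

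- Randomisation and scanning come first.
- Baseline gait is measured, and then the intervention arm is shown visualisations.
- The orthosis is fitted and tuned, with visualisation in the intervention arm and by observation in the other. Gait is measured at the end of tuning.
- Gait is measured at 3 months, followed by visual feedback in the intervention arm.
- Gait is measured at 6 months, followed by visual feedback in the intervention arm.

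Every velocity measurement after baseline therefore follows at least one showing in one arm and none in the other. The Qualitative data section also lists the impact of visualisations among the topics of the closing patient interviews. Patient blinding to the treatment received is ruled out by the design.

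**2. Collector level.** Two people collect the baseline, 3-month and 6-month data.

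- The bioengineer belongs to both teams, attends every session and presents the data, so necessarily knows the arm.
- The third physiotherapist is independent of the teams. Independence is not blinding, and blinding of this person is neither stated nor ruled out. If this person were present when baseline visualisations were shown, the arm would be known at later visits.

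**3. Analysis level.** Blinding is stated in two sections, and nothing contradicts it.

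**4. The plan's own figure.** Inputs from the Sample size section: difference 0.2 m/s, SD 0.24 m/s, 90% power, 5% significance (two-sided assumed).

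- Standardised difference = 0.2/0.24 = 0.833 (the article gives 0.831).
- n per group by the normal approximation = 31, total 62, as stated.
- Power at 31 per group = 90.7% (normal) or 89.8% (t test).
- 70 recruited allows 1 - 62/70 = 11.4% withdrawal, consistent with the stated allowance.

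The sample size reproduces and is not in dispute.

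**5. Illustration of what a bias would do.** The standard error of the arm difference is 0.24 × sqrt(2/31) = 0.061 m/s. Suppose there is no true effect but a systematic bias b between arms. The two-sample t test on 60 degrees of freedom then rejects with a probability given by the noncentral t distribution with noncentrality b/0.061. The values of b are assumptions; the documents give none.

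| Assumed bias b (m/s) | b / SE | b as share of 0.2 m/s | Two-sided rejection rate at nominal 5% |
|---|---|---|---|
| 0.02 | 0.33 | 10% | about 6% |
| 0.05 | 0.82 | 25% | about 13% |
| 0.10 | 1.64 | 50% | about 36% |

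The result runs from negligible to serious, depending almost wholly on b.

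**The case against.** **There is some blinding.** A reader might infer that the primary outcome has no blinding at all. The documents do not support that: the statistical analyst and the assessors comparing data sets are stated to be blinded. The 8-camera motion capture system and force platforms also leave little room for discretion in recording velocity. Both points stand. They protect analysis and scoring, but not patient effort or encouragement during the walk.

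**The third physiotherapist may be blinded.** A reader might infer that both collectors are unblinded. The article is silent on the physiotherapist, and a fuller protocol may settle it, so only the bioengineer's knowledge can be asserted. The article also does not say who scores the two rated scales.

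**Feedback already follows measurement.** This is true of gait at baseline, 3 months and 6 months, so visualisation cannot affect baseline gait, and the 6-month feedback cannot affect any planned gait measurement. It does not remove the effect of earlier showings on later visits.

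**Responding to feedback is part of the treatment.** The Discussion counts explanation and highlighted progress as possible patient benefits. A patient who walks faster because feedback motivates them may be showing a real effect of the package, so it would be wrong to count the whole response as bias. Encouragement from a collector who knows the arm is not part of the package.

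**Patients may only be unaware which arm is experimental.** That would be a defensible claim, but it is not what the article says. It says patients are blinded to the intervention they receive.

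**Patient blinding is not feasible here, and the trial calls itself early and exploratory.** Both are fair. They are reasons to describe the design correctly, not to keep a label that it cannot meet.

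**Conclusion.** The statement that patients are blinded is wrong as written and is contradicted by four other places in the same article. A fuller protocol could not make it true while the intervention stays as described. One of the two outcome collectors necessarily knows the allocation, and the blinding of the other is not stated. Only the statistical comparison is stated to be blinded.

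The contradiction rests on the text alone and needs no assumption. The possible effect on the primary result does need assumptions: that velocity responds to effort and encouragement (an inference, not a statement in the article), that the planning SD of 0.24 m/s applies, and that 31 per group complete. Under these, assumed biases of 0.02 to 0.10 m/s give error rates of about 6% to 36%. No single figure in that range should be read as the trial's actual error rate, because the documents give no bias size and part of any motivational response belongs to the intervention. Randomisation, allocation concealment and the sample size are unaffected.

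**What to change.** 1. Describe the trial as open to patients and treating staff, with blinded analysis, and remove the statement that patients are blinded to their intervention.
2. Require the existing third physiotherapist to be blinded to allocation, to give scripted walking instructions, to score the Modified Ashworth Scale and Modified Rivermead Mobility Index, and to leave before any visualisation is shown.
3. Have EQ-5D completed before feedback at each session where it is collected.
4. During measurement, limit the bioengineer to running the capture. The bioengineer still presents visualisations afterwards. Process velocity from ID-coded files that do not carry the arm.
5. Record the physiotherapist's guess of allocation, and claim blinded outcome assessment only as far as it was achieved.

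The cost is protocol wording and some care over the order of each session, with no new staff and no extra visits. Patients may still reveal their arm to the physiotherapist, so the change lowers the risk of bias without removing it. The trial was ongoing when the article was written. Sessions held after the change can be protected, and those already held should be reported as they were conducted.

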**Figure 1 F1:**
[figure not shown]
**Flow diagram of trial design showing intervention (visualisation) and non-intervention (observation) arms**.

The randomisation sequence will be generated using an independently verified S-PLUS program, by the method of randomised permuted blocks of length four, with participants allocated to interventions in a 1:1 ratio. Researchers will access the random allocations via the study web portal (designed and maintained by The Robertson Centre for Biostatistics at The University of Glasgow) and the sequence will remain concealed until the participant's details are registered on the system.

As patients are recruited to the trial they will be randomly allocated to one of two multidisciplinary teams (MDTs). Each of these MDTs will be made up of a physiotherapist, orthotist and bioengineer. MDT-A will administer the intervention arm of the study, MDT-B will administer the non-intervention arm. In the intervention arm patients will be shown visualisations of their gait patterns and progress throughout the trial. Additionally, the clinicians in MDT-A will also be able to use the gait data and visualisation software to aid their clinical decision making during the AFO tuning session. MDT-B will conduct AFO tuning using standard observational techniques.

Baseline, outcome (3 months) and follow-up (6 months) measurement sessions will be collected by the bioengineer and a third physiotherapist who is independent of the MDTs.

All clinical decision making will be carried out by the physiotherapists and orthotists, while the bioengineer will play a purely technical role collecting data and presenting it to the clinicians and the patient when it is required. The same bioengineer will be used in both MDTs and will be present during all sessions.

Ideally both MDTs would be identical, but this is clearly not possible. Two different MDTs are needed to avoid learning effects in the intervention arm of the study crossing over to the non-intervention and confounding results. In order to balance the MDTs, team members will be selected such that they have similar levels of experience and they will all be required to complete a small amount of basic biomechanics refresher training before the trial commences.

In order to ensure that patients in both arms of the study receive similar AFOs before the tuning stage, a set of design criteria were agreed which both orthotists will follow. These criteria specify the type and thickness of material to be used, angle of ankle dorsiflexion, the pre-tuning shank-to-vertical angle of the AFO when combined with footwear, the trim lines, carbon fibre reinforcements to be used and the positioning/functionality of the straps. See sub-section 'Rigid AFO Design Criteria' for more detail.

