### Participant recruitment (inclusion/exclusion criteria)

The stroke physiotherapy team will identify stroke patients who are suitable for AFO treatment and will notify the researcher of those considered to meet all of the inclusion/exclusion criteria (see Table 1). The researcher will then inform them of the study and if they are interested they will be given a copy of the 'information for participants' sheet to read. The patient will be given a suitable amount of time (minimum of 48 hours) to consider volunteering. During this time they will be free to ask for more information from the researcher about the study and to consult with friends, carers or relatives.

**Table 1 T1:** Participant inclusion and exclusion criteria

Inclusion criteria	Exclusion criteria
Inpatients who have suffered a recent (1-12 months) hemiplegia	Are unable to give informed consent
Aged 16-80 years	Are unable to walk, even when assisted
Male or Female	Suffer from significant peripheral vascular disease ? not suitable for fitting of AFO
Have difficulty walking, but able to walk with/without assistance	Have any other significant medical problems likely to preclude use of AFO or follow-up
Have difficulty flexing knee and extending hip during walking	
Meet the criteria for AFO referral as outlined in AFO screening tool (NHS BPS, Appendix 9)	
Able to give informed consent	
Able to attend for follow-up at 3 and 6 months	

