### Location

Participants will be recruited from the stroke wards at the Southern General Hospital, Glasgow, UK. Baseline, tuning, 3 month and 6 month sessions will all take place at West of Scotland Mobility and Rehabilitation Centre (WestMARC) at the Southern General Hospital, Glasgow, UK.

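### A single fixed block length of four at one unblinded site would let a recruiter who tracks past allocations know about a third of them in advance; undisclosed, randomly varying block lengths would remove most of that certainty

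*Protocol article*

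**What the plan says.** Under Study design, in the text after Figure 1, patients are randomised "by the method of randomised permuted blocks of length four, with participants allocated to interventions in a 1:1 ratio". Four is the only block length given, and no stratification is described. The same paragraph says "Researchers will access the random allocations via the study web portal", a system run by an external biostatistics centre, and adds the safeguard that "the sequence will remain concealed until the participant's details are registered on the system".

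Four other statements bear on who could learn past allocations and who controls enrolment:

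- **Blinding.** Patients are blinded, "however the clinicians involved will not be blinded".
- **Teams.** Each arm has its own team: "MDT-A will administer the intervention arm of the study, MDT-B will administer the non-intervention arm". One person spans both: "The same bioengineer will be used in both MDTs and will be present during all sessions".
- **Site.** Under Location: "Participants will be recruited from the stroke wards at the Southern General Hospital, Glasgow, UK".
- **Recruitment.** Under Participant recruitment, the stroke physiotherapy team "will notify the researcher of those considered to meet all of the inclusion/exclusion criteria". The researcher then approaches the patient, who has at least 48 hours to decide.

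The Study design section gives the minimising of selection bias and confounding as the main benefit of randomising. Trial Status says the trial is ongoing.

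**The concern.** Portal concealment stops staff from looking up the next entry. It does not stop them from working it out. With one known block length and, as described, one list at one hospital, the order of past allocations is enough to fix some future ones.

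The recruitment process leaves some discretion. Several eligibility criteria need judgement, the time window is 1 to 12 months after hemiplegia, and the patient has an open-ended period to decide. A recruiter who knew the next arm could, knowingly or not, influence which patient is registered next. If patients with better or worse expected recovery were placed unevenly, the comparison of walking velocity would carry a bias that the analysis could not fully remove.

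**Working it through.** **The plan's own figures.** The article gives no predictability figure. Its sample size, which supplies the denominator here, reproduces. With a difference of 0.2 m/s, SD 0.24 m/s, 90% power and 5% significance (taken as two-sided), n per group = 2 × (1.960 + 1.282)² × (0.24/0.2)² = 30.3, rounded up to 31, or 62 in total. Seventy allows for 1 − 62/70 = 11.4% withdrawal. Nothing below changes these numbers.

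**Certain allocations with fixed blocks of four.** The six equally likely 1:1 blocks are AABB, ABAB, ABBA, BAAB, BABA and BBAA. An allocation is certain once one arm's two places in the block are used.

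| Place in block | Probability that it is certain | Best-guess success |
|---|---|---|
| 1st | 0 | 1/2 |
| 2nd | 0 | 2/3 |
| 3rd | 2/6 = 1/3 (AABB, BBAA) | 1/3 × 1 + 2/3 × 1/2 = 2/3 |
| 4th | 1 | 1 |

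- Per block: (1/3 + 1)/4 = 33.3% certain. Best guess: (1/2 + 2/3 + 2/3 + 1)/4 = 70.8%.
- Over 70 patients (17 full blocks plus two patients): 17 × 4/3 = 22.7 certain allocations, or 32.4%. Best guess: 17 × 2.833 + 1/2 + 2/3 = 49.3 of 70, or 70.5%.

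**Effect of varying the block length.** Results are from 2,000 simulated trials of 70 patients for each set of lengths. The simulated observer knows the set of possible lengths and every past allocation in order, and updates by Bayes' rule. This is demanding if the lengths really are undisclosed. The sets are illustrative.

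| Block lengths | Certain | Best-guess success |
|---|---|---|
| 4 (current) | 32.4% | 70.5% |
| 4, 6 | 5.5% | 69.1% |
| 2, 4, 6 | 4.1% | 70.1% |
| 4, 6, 8 | 2.3% | 67.8% |

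**Possible size of bias (assumed inputs).** Suppose a share s of the certain allocations is steered, and that prognosis in the steered patients is shifted by 0.12 m/s (half the stated SD) upwards in one arm and downwards in the other. The bias in the difference is s × 0.324 × 0.24 m/s. For s = 25%, 50% and 100% this is about 0.02, 0.04 and 0.08 m/s, against a target of 0.2 m/s. On a smaller assumption, three patients each 0.24 m/s above average and all placed in one arm of 35 shift that arm's mean by 3 × 0.24/35 = 0.02 m/s.

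**Cost in balance.** With 70 patients in fixed blocks of four, the last, incomplete block can leave a difference of two (36 against 34). If the last block has length eight, the difference can reach four (37 against 33). The variance of a difference in means is then (1/33 + 1/37)/(2/35) = 1.003 times the balanced value.

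**The case against.** The strongest reply is that the article does not put the necessary knowledge and control in one person. Exploiting the blocks requires knowing the length, seeing past allocations in registration order, and influencing who is registered when. The stroke physiotherapy team selects patients but is not said to see allocations. Each team's physiotherapist and orthotist serve one arm and are given no recruitment role. The bioengineer attends all sessions but is not said to recruit, and session order need not match registration order. That leaves the researcher who approaches patients, who may be among the researchers using the portal. This objection stands as a limit: the route is plausible but inferred.

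The article is also a condensed account. Stratification is not described, but it may exist in the full protocol and would make tracking harder. Whether the site's working documents give the block length cannot be seen. Baseline gait is measured in everyone, so steering on walking speed would tend to show, although steering on expected recovery would not.

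Three stronger readings are tempting and not supported:

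- A reader might infer that any member of staff can predict allocations. The roles above do not support this, and patients and the assessors analysing the data are described as blinded.
- A reader might take the roughly 71% best-guess rate, against 50% by chance, as harm that varying lengths would remove. The table shows that it hardly moves; what falls is certainty.
- A reader might think that the portal reveals allocations before registration. The article says the opposite.

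**Conclusion.** The concern holds in a limited form. As described, the design would let a recruiter who knows the block length and tracks allocations in order be certain of about one third of them (33.3% per block, about 23 of 70). This assumes a single unstratified list and an overlap between those who see allocations and those who approach patients.

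It would be wrong to conclude that concealment has failed or that selection bias has occurred. Concealment is weakened, not absent, and nothing shows that it would be exploited. Nor does the article claim that randomisation abolishes selection bias; it says the bias is minimised. The bias figures above show scale under assumed steering and are not estimates. There is no numerical error, and the sample size stands. This is a stated design choice that can be improved cheaply.

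**What to change.** For the remaining allocations, have the biostatistics centre generate the sequence with randomly varying block lengths, for example 4, 6 and 8, and not disclose the lengths to recruiting staff. Start the new sequence at the end of a current block of four, so that no extra imbalance is carried over. The existing rule that an allocation appears only after registration already does its job and needs no change.

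Over a full trial of 70 the change would take certain predictions from about 32% to about 2% (about 4% with lengths 2, 4 and 6). Because the trial is under way, the gain applies only to patients not yet randomised, a number the article does not give. Best-guess success falls only slightly, from about 70% to 68%, so the gain should be described as a loss of certainty and not as full unpredictability.

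The cost is a change to the generating program and the portal's list, and a final imbalance of up to about four patients instead of two, with a negligible loss of precision. It needs no extra patients and no change to treatment or analysis.
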